### Component 3: survey of knowledge, attitudes and practice regarding salt intake and estimation of salt consumption levels

The survey will use a nationally representative sample of 1,200 participants aged 18 years or older. We will approach STATIN to select a total of 60 EDs from all 14 parishes, using probability proportionate to size. Within each ED, we will select 20 households and within each household we will select one individual, using the Kish method.
^
31
^

*Inclusion and exclusion criteria*

We will include non-institutionalized adults, aged 18 years and older, resident in the selected ED. We will exclude institutionalized participants or individuals who are unable to complete the questionnaire due to impaired capacity to understand the questions asked or inability to speak. No other health or social condition were considered as inclusion or exclusion criteria. However, we are collecting data on participants use of medications for hypertension and, specifically, if they are using diuretics. We will assess whether there are differences in urine sodium excretion for those with hypertension or on diuretic therapy. Where necessary we will exclude participants on diuretic therapy from analyses or conduct sensitivity analyses with models excluding and including persons on diuretic therapy.

*Recruitment*

For each selected community we will first obtain a map of the community from STATIN and then arrange a visit to the community to establish the number of households and determine the household sampling interval. We aim to select 20 individuals from each ED, one from each household. The household sampling interval will therefore be determined by dividing the number of households by 20. A visit will be made to each selected household and one person will be selected using the Kish method.
^
31
^ For this procedure, the trained data collectors make a list of all the household members who are eligible to participate in the study, ordered by age and sex and the select one person based on a random number system. If the participant from the selected household refuses to participate we will attempt to recruit a participant from the neighboring household. Recruitment will be supervised by the study’s project coordinator.

*Data collection*

For each selected participant, we will first obtain informed consent (verbal or written) and then administer a questionnaire to evaluate knowledge about salt intake and health, attitudes with regards to salt intake and low salt diet, and current practices of salt intake. Where verbal consent is obtained this would be witnessed and signed by the research assistant obtaining consent. This informed consent procedure has been approved by the UWI and the Ministry of Health and Wellness Ethics Committees. The questionnaire and consent form can be found as
*Extended data.*
^
39
^
^,^
^
40
^ The questionnaire was developed based on a review of published questionnaires on dietary salt intake identified through a search of
PubMed (RRID:SCR_004846) and
Google (RRID:SCR_017097).
^
34
^
^–^
^
36
^ Questions were adapted to ensure cultural appropriateness for the Jamaican context.

In addition to the questions on knowledge attitudes and practices regarding salt intake, we will also administer a partial food frequency questionnaire (FFQ) to assess frequency of consumption of high salt foods and compare this with the frequency of consumption of low salt or other healthy foods. The FFQ was derived from a local FFQ which was previously validated for use in Jamaica.
^
37
^ The FFQ has undergone several updates using 24-hour recalls to calibrate food listings and capture detailed use of sodium and related food preparation practices. Instruments have been used successfully in a sodium reduction trial (Jamaica) and a more recent Barbados study of ultra-processed food (UPF) intakes.
^
27
^
^,^
^
38
^

Additional questionnaire items will include physical activity and smoking practices as measures of other health behaviors. Physical activity will be assessed using the
English version of the Short International Physical Activity Questionnaire (IPAQ), which is now in the public domain. The full questionnaire (including sections on knowledge, attitudes and practices, food frequency and physical activity) was pre-tested to ensure accuracy and acceptability within the Jamaican context. Pre-testing involved the administration of the questionnaire to approximately 20 individuals who fit the project’s inclusion criteria and assess time taken to administer the questionnaire, making note of any difficulty with answering specific questionnaire items and ask for specific feedback on the questionnaire. Adjustments were then made to improve understandability and acceptability. We will also measure weight, height, waist circumference, hip circumference and blood pressure and collect an early morning, or casual, spot urine sample to measure urine sodium excretion. Instructions for collecting the urine sample will be given at the time of recruitment into the study. Urine sodium will be measured using the Roche 9180 Electrolyte Analyzer (Mannheim, Germany) at the Tropical Metabolism Research Unit laboratory.

*Coronavirus disease 2019 (COVID-19) considerations*

Field work for this component began in the first quarter of 2022. Interviews for questionnaire administration are completed
*via* telephone to minimize person to person contact. In light of the COVID-19 pandemic we have instituted contact precautions in keeping with the Mona Research Ethics Committee Guidelines on conducting face-to-face research in light of COVID-19. Specifically, we will require all data collectors to wear masks and practice appropriate hand sanitization and handwashing during recruitment and measurement. Respondents will also be required to wear masks during the interactions with data collectors. We will provide disposable masks for respondents where necessary. All data collectors are encouraged to receive the COVID-19 vaccine prior to the beginning of data collection.

*Sample size and power*

Sample size was calculated using the
*‘power onemean’* command in Stata. Using the mean of 2,656 mg/day from the Barbados Health of the Nation Study as outlined above
^
26
^ and a 7.5% margin of error (
*i.e.*, 2,656 vs. 2,457), the required sample size with alpha 0.05 and power 80% was estimated as 511. Given the design effect of 1.94 as calculated above, the minimum sample size accounting for survey design would be 991. We will target a sample size of 1,200 participants (20% above the minimum sample size) to allow for participant non-response and missing data.

*Data management*

Data will be collected by trained data collectors using password-protected tablet computers, with
REDCap (RRID:SCR_003445) data collection software. We will include range and consistency checks to minimize data entry errors. Data collected on the tablets will be protected using data encryption. Options to transfer data to external drives (
*e.g.*, USB flash drives and SD cards will be disabled. Data will then be uploaded to a secure server using data encryption protocols. Deidentified data will then be downloaded for analysis. Access to data will be limited only to members of the study’s data analysis team. De-identified data will be kept indefinitely. Identifiable data, such as consent forms will be kept on secure encrypted servers and will be destroyed by permanent deletion from the server after five years. To assess data accuracy and reliability of data, we will have project staff recollect data from 5–10% of respondents to check against the original collected data.

*Statistical analyses*

From these data we will estimate the proportion of participants reporting appropriate knowledge on the effects of salt on health, and the proportion of participants with various attitudes and practices regarding salt intake. We will also obtain mean urine sodium concentration and estimate 24-hour urine sodium using the PAHO (Equation 1) equations. We will also explore the development of a new equation for use in Jamaica and similar populations from our validation study in ‘
*Component 4*’, outlined below. We will then estimate the proportion of patients with high dietary sodium consumption. We will also evaluate how dietary sodium consumption, knowledge, attitudes and practices vary by sex, other sociodemographic factors, and biomedical characteristics, including blood pressure levels and hypertension awareness. The analyses for the evaluation of knowledge attitudes and practices will be primarily descriptive, but we will use scores to classify persons in KAP categories. These categories will be created in the analysis phase of the study. Multivariable regression models will be used to identify factors associated with high sodium intake and with good knowledge, attitudes, or practices related to salt intake. Analyses will be weighted to account for survey design.

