### Component 1: spot urine sodium analyses

*Data sources*

Data from 1,091 spot urine sodium samples, along with relevant sociodemographic and biomedical data were obtained from the third Jamaica Health and Lifestyle Survey (JHLS-III), which was conducted between September 2016 and February 2017.
^
3
^ Some details on the procedures used in JHLS-III have been published.
^
29
^ The survey enrolled a nationally representative sample of Jamaicans 15 years and older using a multi-stage sampling design. In the first stage, 171 enumeration districts (EDs) were randomly selected from a national total of 6,241 EDs, with selection probability proportionate to the size of the ED. In the second stage, 20 households (dwellings) are systematically selected within each ED, using a random starting point. Within each household one individual is selected using the Kish method.
^
31
^ The survey collected data on a wide cross-section of health issues using questionnaires, physical measurements, point-of-care and laboratory measurements and geo-informatics (GIS) mapping. An early morning spot urine sample was collected from study participants and urine sodium measured using the Roche 9180 Electrolyte Analyzer (Mannheim, Germany). These data along with relevant sociodemographic data and data on hypertension and risk factors or comorbidities were obtained from the JHLS-III Research Group. The specific variables included are available as Extended Data. JHLS-III previously received ethical approval from the UWI (Mona) Ethics Committee (ECP 25, 15/16) and the Ministry of Health Ethics Committee (Study Number 2015/51).

*Inclusion and exclusion criteria*

For this component we will include participants from JHLS-III who have available data for urinary sodium. We will exclude participants with missing data on urinary sodium, age, or sex.

*Sample size and power*

Given that we have a fixed available sample size we estimated the power for the 1,091 available urine sodium samples. A design effect for the survey was calculated given the multistage sampling procedure. This was done by calculating the ratio of the variance of the urinary sodium values in samples from JHLS-III with and without accounting for survey design. The estimated design effect was 1.94. Using this design effect our sample of 1,091 participants translates to an effective sample size of 563 participants. Hypothesized mean sodium excretion was obtained from the Health of the Nations Study in Barbados.
^
26

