^ Mean sodium intake in that study was 2,656 mg per day. Using the ‘
*power onemean’* command in
Stata (RRID:SCR_012763) and 10% margin of error (
*i.e.*, 2,656 vs. 2,390), the effective sample size of 563 gave a power of 97.5%.

*Statistical analyses*

From these data we will estimate mean dietary sodium consumption and the proportion of patients with high dietary sodium consumption. The PAHO formula will be used to estimate 24-hour urine sodium and potassium.
^
23
^

The PAHO formula uses measured spot urine sodium or potassium divided by measured spot urine creatinine multiplied by estimated 24-hour urine creatinine as shown below.
^
32
^
^,^
^
33
^ The 24-hour urine creatinine was estimated using the Chronic Kidney Disease Epidemiology Collaboration (CKD-EPI) formula.
^
32
^
^,^
^
33
^

Equation 1. PAHO formula for 24-hour urine sodium.

$$\left[\text{Estimated}\;24-\text{hour value}=\left(\text{measured spot urine}\;\mathrm{Na}\;\text{or}\;K÷\text{measured spot urine}\;\mathrm{Cr}\right)\times \text{estimated}\;24-\text{hour urinary}\;\mathrm{Cr}\right].$$

Equation 2. CKD-EPI formula for 24-hour urine creatinine.

$$\left[\text{Estimated}\;24-\text{hour urine}\;\mathrm{Cr}=879.89+12.51\times \text{weight}\;\left(\mathrm{kg}\right)-6.19\times \mathrm{age}+\left(34.51\;\text{if black}\right)-\left(379.42\;\text{if female}\right)\right]$$

Note: PAHO, Pan American Health organization; CKD-EPI, Chronic Kidney Disease Epidemiology Collaboration; Cr, creatinine; BMI, body mass index; Na, sodium; K, potassium.

We will also estimate how dietary sodium consumption vary by sex and other sociodemographic factors, self-reported dietary practices, and biomedical characteristics, including blood pressure levels and hypertension awareness. Multivariable regression models will be used to identify factors associated with high sodium intake. Analyses will be weighted to account for survey design.

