### Component 4: validation study using 24-hour urinary sodium

A 10% sub-sample from ‘
*Component 3*’, described above, will be asked to provide a 24-hour urine sample to measure 24-hour urine sodium excretion to assess the accuracy of spot urine sodium estimation and the correlation between spot urinary sodium and 24-hour urinary sodium. The sub-sample will consist of participants from the first six EDs to be recruited for the survey in ‘
*Component 3*’. All participants from these first six EDs will be included. We will exclude participants who are unwilling to carry out the 24-hour urine collection. If we have less than 120 participants from the first six EDs, we will continue to recruit from the next EDs until the targeted sample of 120 individuals is reached. We will estimate 24-hour urine sodium from the spot urine sodium and then assess the levels of agreement between 24-hour urine sodium estimated from spot urinary sodium and 24-hour urinary sodium from the 24-hour urine sample. Data from this validation study will be used to calibrate equations for estimating 24-hour urinary sodium from spot urinary sodium measurements. These new equations from local data may then be used for this and future studies on urine sodium excretion.

The procedure for collecting 24-hour urine sample will be as follows: On the morning of the start of the 24-hour period, the participant must urinate to completely empty the bladder and record the start time. This “first-pass urine” is discarded. Subsequently all urine passed is collected in a container, including the first urine of the following morning. This should be at the same time as the previous morning to ensure 24 hours is completed. The time the final urine sample is passed is recorded. The container with the 24-hour urine sample will be collected from the participant later that morning. The information sheet for the 24-hour urine collection can be found as
*Extended data.*
^
42
^

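### Component 3 accepts either an early-morning or a casual spot urine, and Component 4 inherits this, so its agreement statistics and any calibrated equation would describe an unspecified mix of specimens

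*Protocol article*

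**What the plan says.** - Component 1 (Data sources), on the 2016-2017 survey: "An early morning spot urine sample was collected from study participants".
- Component 3 (Data collection): the study will "collect an early morning, or casual, spot urine sample to measure urine sodium excretion". No preference between the two is stated. Instructions for the sample are given at recruitment, but their content is not in the article.
- Component 4: a 10% sub-sample of Component 3, "described above, will be asked to provide a 24-hour urine sample to measure 24-hour urine sodium excretion". The section sets no separate rule for the spot sample. It continues: "We will estimate 24-hour urine sodium from the spot urine sodium and then assess the levels of agreement".
- Component 4, on use of the results: "Data from this validation study will be used to calibrate equations for estimating 24-hour urinary sodium from spot urinary sodium measurements", and "These new equations from local data may then be used for this and future studies on urine sodium excretion".
- Component 1 (Statistical analyses): Equation 1 divides spot sodium or potassium by spot creatinine and multiplies by an estimated 24-hour creatinine. For that last part, "The 24-hour urine creatinine was estimated using the Chronic Kidney Disease Epidemiology Collaboration (CKD-EPI) formula", with weight, age, race and sex as inputs.
- Component 3 (Statistical analyses) applies the same method: "We will also obtain mean urine sodium concentration and estimate 24-hour urine sodium using the PAHO (Equation 1) equations".

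The only times the article says are recorded are the start and end of the 24-hour collection. The only adjustment named in Component 4 is for physical activity.

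**The concern.** The estimate takes its sodium information from one void, through the ratio of sodium to creatinine. If that ratio differs on average between an overnight void and one passed later in the day, a participant's estimate depends on which was supplied, and nothing in Equations 1 and 2 absorbs the difference.

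Objective 4 asks how accurate spot urine is in Jamaica. Under the either/or rule the answer applies to whatever blend of voids the validation participants happened to give. An equation fitted to that blend carries the blend into its coefficients. The validation sample comes from the first six of 60 EDs, so its blend need not be that of the remaining 54. It is not that of Component 1, which has no casual voids, and a later survey may have another again. In Component 3, the planned comparisons of sodium intake between groups could also pick up differences in void type, if void type differs between those groups.

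**Working it through.** **1. The plan's own figures.** For Component 4, the Fisher z formula with two-sided alpha 0.05 and 80% power (both assumed, as the section states neither) is n = [(1.960 + 0.842) / (atanh r1 − atanh r0)]² + 3.
- 0.40 against 0.65: (2.802 / 0.3517)² + 3 = 66.5, so 67. Stated: 67.
- 0.40 against 0.60: (2.802 / 0.2695)² + 3 = 111.1, so 112. Stated: 112.

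These figures reproduce, and neither depends on void type. The issue is what is measured, not the arithmetic.

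**2. The specimen at each step.**

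| Step | Spot specimen | Void-time term |
|---|---|---|
| Component 1 estimate | early morning | none |
| Component 3 estimate | early morning or casual | none |
| Component 4 agreement and calibration | as Component 3 (inferred from the sub-sample design) | none named |
| Onward use of a new equation | not specified | none named |

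**3. Shift in a mean (illustration only).** Let p be the share of casual voids and d the relative difference between casual and early-morning estimates. The document gives neither. Against an all-early-morning sample, the mean shifts by p × d. On the planning mean of 2,656 mg/day:
- p = 0.25, d = 5%: 1.25%, about 33 mg/day
- p = 0.50, d = 10%: 5%, about 133 mg/day
- p = 0.75, d = 20%: 15%, about 398 mg/day

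The sign of d is unknown. The shift is a difference from another specimen, not a demonstrated bias against 24-hour excretion.

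**4. Transfer of a calibrated equation (illustration only).** If the equation is calibrated where the casual share is p4 and applied where it is p, the level error is roughly (p − p4) × d.
- Same mix (p = p4): about zero.
- p4 = 0.50, other EDs p = 0.25, d = 10%: about −2.5%, or 66 mg/day.
- p4 = 0.50, applied to Component 1 (p = 0), d = 10%: about −5%, or 133 mg/day.

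**5. Effect on the validation correlation (illustration only).** Take r = 0.60 within each void type, n = 120, and a level difference of k within-type standard deviations in the spot estimate. The pooled correlation is 0.60 / √(1 + p(1 − p)k²). Power is against a null of 0.40.
- k = 0: r = 0.60, power 83%
- k = 0.5, p = 0.5: 0.60 / √1.0625 = 0.58, power about 74%
- k = 1, p = 0.5: 0.60 / √1.25 = 0.54, power about 48%

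**6. Limit on splitting.** An even split of 120 leaves 60 per void type, before the exclusions for volume, collection time and creatinine. That is below both 67 and 112, so separate validations by void type would not meet the plan's own targets.

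**The case against.** The strongest reply is that the article is a condensed account. The collection instructions, questionnaire and data-capture forms are not shown, and they may make early morning the default, with casual as a fallback, or may record the time of void. The order of words in Component 3 fits that reading. For Component 3 itself, validation on specimens collected under the same rule is also the relevant validation, provided the mix in the first EDs resembles the rest. Both points stand, and they limit the finding. They do not remove it: the article itself sets an either/or rule and an equation for reuse, with nothing linking the two.

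A reader might infer more than the document supports:
- **That void type follows convenience and so tracks age, sex, work or district.** This is plausible, but no section says how the void is chosen.
- **That the mixture could use up the whole 7.5% difference on which Component 3 is sized.** Half casual with a 15% difference gives 0.5 × 15% = 7.5%, or 199 mg/day, but only because those two values were picked.
- **That the 2016-2017 and later national estimates will be compared, or that Component 1 will be recalibrated.** Neither is planned. A new equation is to be explored and may be used.
- **That early-morning urine is the better specimen.** Nothing in the document shows that it lies closer to 24-hour excretion, so requiring it is not the evident remedy.

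**Conclusion.** The point holds as a measurement and transportability problem. Followed as written, the plan permits two specimen types in Components 3 and 4, has no term that separates them, and would produce agreement statistics and possibly an equation with no defined target specimen. Component 1's own mean, under the existing equation, is not affected.

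That Component 4 uses the mixed specimen is an inference from its being a sub-sample of Component 3. The size and direction of any effect are unknown, and the figures under steps 3 to 5 of the working rest on assumed shares and differences. If void type makes no difference to the estimate, or if nearly all samples are of one type, the consequence is negligible. Without void type on record, the study could not show which of these is the case. It is worth correcting because the remedy is cheap and Objective 4 depends on it.

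**What to change.** - **Component 3, Data collection:** record void type and clock time for every spot sample. Keep one collection rule in all EDs. Fieldwork has begun and Component 4 draws on the first six EDs, so a stricter rule for the remaining EDs only would tie void type to ED and calendar time and separate the validation sample from the rest.
- **Component 4:** include void type (or time) as a term in the calibration equation. Report bias and agreement overall and descriptively by void type, and say that subgroup precision is limited with 120 people.
- **Component 3, Statistical analyses:** include void type as a covariate in the regression models for sodium intake.
- **Component 1:** apply a new equation only with its early-morning term, or if it was derived from early-morning samples.
- **Limitations:** if samples already taken lack void type, say so.

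The cost is one extra form field, one extra model term, and missing void type for early samples. No sample-size figure changes.

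### The Component 3 minimum of 991 at 80% power is not supported, because a design effect from a survey averaging about 6 urine values per ED is applied unchanged to 20 per ED

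*Protocol article*

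**What the plan says.** The design effect is derived under Component 1 of the protocol article. JHLS-III drew its sample in stages: "In the first stage, 171 enumeration districts (EDs) were randomly selected from a national total of 6,241 EDs", then 20 households per ED and one person per household by the Kish method. Urinary sodium is available for 1,091 people. The design effect is the ratio of the variance of those values with and without allowance for the survey design: "The estimated design effect was 1.94". It is a single total figure. The article does not separate clustering from weighting, gives no ICC, and does not say how many EDs supplied urine.

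Component 3 uses 60 EDs: "Within each ED, we will select 20 households and within each household we will select one individual". Its sample size takes the Barbados mean of 2,656 mg/day and what the article calls a "7.5% margin of error" (2,656 vs. 2,457), and reports that "the required sample size with alpha 0.05 and power 80% was estimated as 511". That number is multiplied by 1.94: "Given the design effect of 1.94 as calculated above, the minimum sample size accounting for survey design would be 991". The target of 1,200 is described as about 20% above the minimum, to cover non-response and missing data. The change in the number of people per ED is not mentioned.

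**The concern.** For roughly equal clusters, a design effect is approximately w × (1 + (m − 1) × ICC), where w is the part due to unequal weights and m is the number of observations per ED. Only w can be carried from one survey to another without looking at m. JHLS-III averaged 1,091 / 171 = 6.4 urine values per selected ED, while Component 3 plans 20. Unless the ICC is zero, or the urine values came from far fewer EDs than 171, the design effect in Component 3 exceeds 1.94.

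At stake are the two planning figures for the main survey, the minimum of 991 and the 80% power. The margin between 991 and 1,200 does not answer this, because the article assigns it to non-response and missing data. If clustering uses it up, nothing is left for those losses.

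**Working it through.** **Inputs from the article.** Component 3: 2,656 vs. 2,457 mg/day (difference 199), alpha 0.05, power 80%, n = 511, 60 EDs, 20 per ED, target 1,200. Component 1: 2,656 vs. 2,390 mg/day (difference 266), 1,091 urine values, 171 EDs, design effect 1.94, effective n 563.

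**Assumptions.** The test is two-sided (not stated). The SD is not given and is solved for. The weighting part w is the same in both surveys. Urine values per ED are roughly equal.

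**Step 1: reproduce the plan's figures.**
- SD from Component 3: 199 × √511 / (1.960 + 0.842) ≈ 1,606 mg.
- SD from Component 1, where "the effective sample size of 563 gave a power of 97.5" per cent: 266 × √563 / (1.960 + 1.960) ≈ 1,610 mg.
- The two agree. With SD 1,603, n = 511 gives 80.1% and n = 563 gives 97.6%. This SD is used below.
- 511 × 1.94 = 991.3, and 1,200 / 991 = 1.21. The article's multiplication is correct.
- On the stated design effect, power is 80% at 991 and 87% at 1,200.

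**Step 2: recompute the design effect at 20 per ED.** With m = 1,091 / 171 = 6.38:
- ICC = (1.94 / w − 1) / 5.38
- Design effect at 20 = w × (1 + 19 × ICC)
- Required n = 511 × design effect
- Power at 1,200 = Φ(199 × √n_eff / 1,603 − 1.96), with n_eff = 1,200 / design effect
- 95% CI half-width = 1.96 × 1,603 / √n_eff

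| What 1.94 consists of | w | ICC | Design effect at 20 | Required n | n_eff of 1,200 | Power | Half-width |
|---|---|---|---|---|---|---|---|
| All weighting | 1.94 | 0 | 1.94 | 991 | 619 | 87% | 126 mg (4.8%) |
| Break-even | 1.78 | 0.017 | 2.35 | 1,200 | 511 | 80% | 139 mg (5.2%) |
| Mostly weighting | 1.60 | 0.040 | 2.80 | about 1,430 | 428 | 73% | 152 mg (5.7%) |
| Half weighting (log scale, w = √1.94) | 1.39 | 0.073 | 3.33 | about 1,700 | 361 | 65% | 165 mg (6.2%) |
| All clustering | 1.00 | 0.175 | 4.32 | about 2,200 | 278 | 54% | 189 mg (7.1%) |

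Break-even: 1,200 keeps 80% power only while the design effect is at most 1,200 / 511 = 2.35. Solving (1 + 19r) / (1 + 5.38r) = 2.35 / 1.94 gives r ≈ 0.017. This assumes that nobody is lost.

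**Step 3: vary the number of EDs that supplied urine.** With w = 1, m = 1,091 / k and ICC = 0.94 / (m − 1):

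| EDs with urine (k) | m | ICC | Design effect at 20 | Power at 1,200 |
|---|---|---|---|---|
| 55 | 19.8 | 0.050 | 1.95 | 87% |
| 60 | 18.2 | 0.055 | 2.04 | 85% |
| 90 | 12.1 | 0.085 | 2.61 | 76% |
| 171 | 6.4 | 0.175 | 4.32 | 54% |

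With 90 EDs and half weighting, power is about 80%.

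**Step 4: allow for losses.** If 991 people complete, spread over 60 EDs, m = 991 / 60 = 16.5. All clustering then gives a design effect of 1 + 15.5 × 0.175 ≈ 3.71, n_eff 267, power about 53% and half-width about 192 mg (7.2%). Half weighting gives power of about 62%.

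**The case against.** The strongest reply is that about 6 per ED is an inference. The 171 EDs are those selected for the whole survey, and JHLS-III took 20 households per ED, as Component 3 does. If urine came from only about 55 to 60 EDs, 1.94 roughly transfers. This stands, and the article does not settle it. But 171 × 20 = 3,420 households, and the 1.94 was computed on 1,091 urine values, so the matching second stage does not by itself give equal cluster sizes.

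The all-clustering case is also only a bound. Kish selection of one person per household gives unequal weights, so some of 1.94 is probably weighting. Uneven urine numbers per ED would raise the effective cluster size above 6.4 and shrink the inflation. This also stands.

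A reader might infer that the 80% power is definitely not delivered. The documents do not support that: the weighting share and the number of contributing EDs are unknown, and 80% lies inside the range.

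A reader might also infer that the national mean will be less precise than the article claims. That is not supported either. The half-widths of 126 to 189 mg at 1,200, and about 192 mg at 991 in the worst case, all lie inside the stated 7.5% (199 mg).

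Finally, the power belongs to a one-sample test against the Barbados mean, which the analysis sections do not describe, so losing that power harms the study less than the figures suggest. This limits severity. It does not make the published 991 and 80% supported. Analyses will be weighted for the survey design, so no bias in the estimate follows from the planning figure.

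**Conclusion.** The point holds as an unsupported planning figure, not as an arithmetic error. The 991 and its 80% power rest on a total design effect whose clustering part depends on cluster size, carried without comment from a mean of 6.4 per selected ED to 20 per ED.

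If urine came from most of the 171 EDs in roughly equal numbers, any positive ICC makes the true minimum exceed 991, and 1,200 gives less than 80% power once the ICC passes about 0.017. Power at 1,200 then runs from 87% through about 65% to the 54% bound. If about 55 to 60 EDs contributed, the stated figures are approximately right. All of this rests on the solved-for SD of about 1,603 mg and on equal weighting effects in the two surveys.

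Two lesser matters add no severity. The 1.94 appears to be for spot urinary sodium rather than estimated 24-hour sodium. The 7.5% and 10% figures are detectable differences, not margins of error. Overall this should be fixed, and the fix is a restatement.

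**What to change.** Using the JHLS-III data already in hand:

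1. Report how many EDs supplied urine values and how many values each supplied.
2. For estimated 24-hour sodium, split the design effect into its weighting part and its ICC.
3. Recompute the design effect at 20 per ED.
4. Restate the Component 3 minimum sample size, the power at 1,200, and the expected 95% CI half-width at 1,200 (126 to 189 mg, or 4.8% to 7.1%, over the range worked above). Keep the allowance for non-response and missing data separate from any allowance for clustering.
5. In Components 1 and 3, call the 10% and 7.5% figures detectable differences, and give the expected half-width as the precision. For Component 1 this is 1.96 × 1,603 / √563 ≈ 132 mg (5.0%).

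The cost is one re-analysis and two rewritten sample-size paragraphs. No extra enrolment or change to fieldwork is needed. The stated power may become less favourable.
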